#### **2.2.2. Secondary outcomes**

Clinical score (neurological deficit) using the NIHSS at 7 days and 3

Functional scale (modified Rankin score) at 7 days

Autonomy scale (Barthel score) at 7 days and 3 months

Percentage of patients back home at 7 days and 3 months

Length of stay

Prevalence of swallowing disturbances, pneumopathy, urinary tract infection, bladder catheterization, deep vein thrombosis during hospitalization

Side effects of upright positioning in the two groups= tolerance of early sitting (prevalence of side effects)

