### **2.2. SECONDARY AIMS AND EVALUATION CRITERIA**

#### **2.2.1. Secondary aims**

To show that neurological deficits observed at 7 days and 3 months after stroke onset are improved in the « early sitting » group.

To show that the functional prognosis at 7 days after stroke onset is improved in the « early sitting » group.

To show that autonomy is improved at 7 days and 3 months in the « early sitting » group

To show that early sitting facilitates the process of going back home

To show that the length of stay is shorter in the « early sitting » group

To show that early sitting decreases the rate of complications related to immobilization.

To explore the tolerance of upright positioning in the two groups

To explore the prevalence of fatigue at 3 months after stroke in both groups.

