### ***4.4. EXCLUSION CRITERIA***

- Upfront severe stroke (malignant infarction, not alert with a GCS<13, cerebral herniation on imaging, vital prognosis at stake, NIHSS≥22)
- Fluctuating neurological deficit (increase/ decrease of the NIHSS of 4 points)
- Minor neurological deficit defined by isolated facial palsy (+/- dysarthria), isolated hemianopia, isolated sensitive deficit
- Known intra-cranial arterial stenosis >50%, symptomatic of the new symptomatology

- - History of neurological worsening in association with upright positioning
- - Situation that may alter the tolerance of early sitting: unstoppable vomiting or difficulty in breathing - Patient non autonomous before hospitalization (defined by a Rankin score>3, can't walk without assistance)
- - Deep vein thrombosis or suspicion.
- - Contra indication for early sitting, particularly in case of fracture
- - Patient of legal aged, with a legal guardian
- - Anticipated difficulty with the follow up
- - Participation to another clinical trial
- - Pregnant or breast feeding women
- - Patients who can't speak French
- - Not willing to sign the inform consent form

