### 7 day visit (or before exiting the hospital if before D7)

Will be documented:

- Clinical data

- NIHSS
- Rankin score
- Barthel score

Exit of the hospital:

- Cause of the cerebral infarction, if available
- Internal carotid artery status (ultra sounds)
- Date
- Orientation of the patient (back home, rehabilitation, ...)
- Immobility related complications during hospitalization

3 month visit

Will be documented:

- Clinical data
  - NIHSS
  - Rankin score
  - Barthel score
- Cause of the cerebral infarction
- Presence/Absence of post stroke fatigue
- Synthesis about complications that occurred during the hospital stay

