#### Secondary outcome

- Clinical score (neurological deficit) based on the NIHSS at 7 days and 3 months: comparison of the mean scores between the two groups using a Student's test.
- Functional scale (Rankin score) at 7 days: comparison of the proportions of patients with a score [0-2] by a Chi square test.
- Autonomy scale (Barthel index) at 7 days and 3 months: comparison of the proportions of patients with a score < 60 (dependent) between the 2 groups using a Chi square or a Fisher test
- Length of stay: comparison of the means between the two groups using a Student's test
- Percentage of patient back home before 7 days or 3 months: Chi square test or Fisher test.
- Side effects associated with sitting in the two groups (tolerance of upright positioning in the early versus progressive arms) : description of the side effect in the 2 groups and comparison of the most frequent (>5%) by a Chi square test or a Fisher test.

- Prevalence of swallowing disturbance, pneumopathy, acute urinary retention, bladder catheterization, deep vein thrombosis during hospitalization: comparison between the two groups using a Chi square test or a Fisher test.
- Prevalence of post stroke fatigue: comparison between the two groups using a Chi square test or a Fisher test.

A multivariate logistic regression model will be used in a second step to adjust on age and former (before the qualifying event) Rankin score.

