### **6.2.2. Statistical justification for the number of patients required**

In a meta-analysis of two pilot studies comparing an « early » to a « usual » mobilization procedure, Craig and coll. (9) showed that the percentage of patients with a Rankin score [0-2] was 34.7 % at 3 months in the « usual » group (n=49) versus 57.4 % in the « early » group (n=54).

In our study, we hypothesized that the functional outcome at 3 months assessed by the Rankin score will be better in the « early » group than in the « progressive » group, with a percentage of Rankin [0-2] of 35% in the « progressive » group and 50% in the « early » group. With an alpha risk of 5% and a power of 80% (bilateral), 183 patients per group are required to show a difference. Total number will then be 366 patients.

Percentage of poor tolerance during the first sitting is estimated between 5 and 10% in the 2 groups. As this may affect the Rankin score at 3 months, the number of patient to include has been increase to 400.

If the superiority of the « early » group is not statistically demonstrated, a switch to non inferiority could be undertaken. For this analysis, the non inferiority threshold is set at -5 % (maximum acceptable clinical difference). With 400 patients, non inferiority will be demonstrated if the real difference between the two groups is between 9 and 15%.

Reference: Committee for Proprietary Medical Products (CPMP). Points to consider on switching between superiority and non inferiority. 2000. European Medical Agencies (AMEA). CPMP/EWP/492/99.

The study will be undertaken in 11 centers. Each one, has the potential to recruit patients, with at least 300 cerebral infarction cases a year.

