### **Associated with the pathology :**

- Nausea/Vomiting
- Blood pressure surge persistent on a second measurement, with a BP increase of at least 40mmHg and above 180/100
- Sensation of passing out (linked to a vagal reaction (bradycardia, nausea, sweating) / Hypotensive / other)

- Fall that can be associated with traumatic brain injury or other orthopedic complications (fracture, luxation, sprain)
- Neurological worsening (aggravation of the existing deficits or occurrence of new ones)
- Seizure
- Alteration of consciousness
- Coma
- Death in direct association with the disease (extension of the infarcted zone, cerebral hemorrhage, cerebral edema, herniation), or indirectly linked to the disease (cardiac failure, lung embolism, sepsis, pneumopathy with hypoxia,...)
- Headache
- Swallowing disturbances
- Pneumopathy
- Deep vein thrombosis

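### The complication outcome counts prevalence over the hospital stay, with no onset rule and no listed baseline status, so cases present before randomisation can dilute any effect of early sitting

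*Protocol*

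**What the plan says.** The aim in section 2.2.1 is a preventive one: "To show that early sitting decreases the rate of complications related to immobilization". The matching outcome in section 2.2.2 is "Prevalence of swallowing disturbances, pneumopathy, urinary tract infection, bladder catheterization, deep vein thrombosis during hospitalization". Section 6.2.1 compares the arms by a chi-square or Fisher test on "Prevalence of swallowing disturbance, pneumopathy, acute urinary retention, bladder catheterization, deep vein thrombosis during hospitalization", followed by a logistic model that adjusts for age and pre-stroke Rankin score. The abstract repeats both lists.

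On collection, section 5.2 asks at hospital exit for "Immobility related complications during hospitalization", and at three months for a summary of complications from the stay. The inclusion visit lists symptoms, NIHSS, Rankin, Barthel, risk factors and current treatments. Neither it nor the schedule table names swallowing, infection or catheter status.

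One component is dealt with at entry: section 4.4 excludes "Deep vein thrombosis or suspicion". Section 7.2 lists "Swallowing disturbances", pneumopathy and deep vein thrombosis among the effects of the stroke itself, and lists the same three as complications of immobility in the progressive arm.

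**The concern.** An outcome meant to show prevention should count events that the allocated procedure could have prevented. Here the count runs over the hospital stay, and the stay can begin before randomisation. Sections 4.1 and 4.3 admit patients who reach the neurology unit on the day of onset or the day after, possibly by way of the emergency room or another unit.

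Read as written, swallowing disturbance found on admission, or a catheter placed before allocation, counts in the same way as an infection that begins several days into the stay. Only the last could have been changed by the arm. If earlier cases are common, a real reduction in new complications could be missed, and a non-significant result could be read as evidence that early sitting does nothing for complications. Fewer complications is one of the hypotheses in the protocol's introduction.

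**Working it through.** **The plan's own figure.** The protocol gives no power or effect size for complications. Its only sample size is for the primary outcome: "With an alpha risk of 5% and a power of 80% (bilateral), 183 patients per group are required to show a difference", "with a percentage of Rankin [0-2] of 35% in the « progressive » group and 50% in the « early » group". With mean proportion 0.425 and difference 0.15:

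m = [1.96·√(2·0.425·0.575) + 0.8416·√(0.35·0.65 + 0.50·0.50)]² / 0.15² = 169.3

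With continuity correction: (m/4)·[1 + √(1 + 4/(m·0.15))]² = 182.4, so 183 per group. The stated figure reproduces and is not in question.

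**Inputs for the complication outcome**
- From the protocol: 200 per arm (section 4.1) and 5% significance (section 6.2.3), taken as two-sided.
- From section 1.1: in-hospital rates of 15.5% (urinary tract infection) and 8% (pneumopathy) in a cited cohort. I assume these are new-case rates in the progressive arm. The source reports them for the stay, so they may themselves include earlier cases.
- Assumed: early sitting halves new cases.
- Assumed, because the protocol is silent: a share b already affected at entry, from 0 to 30%.

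**Formulas.** With new-case rate i, the observed prevalence in an arm is p = b + (1 − b)·i. The difference between arms is therefore (1 − b)·(iC − iE). With n per arm and mean proportion p̄:

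power = Φ{ [ |pC − pE| − 1.96·√(2p̄(1 − p̄)/n) ] / √[ (pC(1 − pC) + pE(1 − pE))/n ] }

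The alternative counts new cases among patients free at entry, with n = 200(1 − b) per arm and rates iC and iE.

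**One case in full (b = 10%, 15.5% halved to 7.75%).** pC = 0.10 + 0.90·0.155 = 0.2395 and pE = 0.10 + 0.90·0.0775 = 0.16975. The difference is 0.06975 and p̄ = 0.2046. The null standard error is 0.04034 and the alternative one 0.04019. Power = Φ[(0.06975 − 0.07907)/0.04019] = Φ(−0.232) = 40.8%. Among the 180 per arm free at entry, it is 63.2%.

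**New cases 15.5% v 7.75%**

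| b at entry | Observed prevalence | Ratio | Power, all cases | Free at entry, per arm | Power, new cases |
|---|---|---|---|---|---|
| 0% | 15.5% v 7.75% | 0.50 | 67.8% | 200 | 67.8% |
| 5% | 19.7% v 12.4% | 0.63 | 51.8% | 190 | 65.5% |
| 10% | 24.0% v 17.0% | 0.71 | 40.8% | 180 | 63.2% |
| 20% | 32.4% v 26.2% | 0.81 | 27.5% | 160 | 58.1% |
| 30% | 40.9% v 35.4% | 0.87 | 19.9% | 140 | 52.5% |

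**New cases 8% v 4%.** Power is 39.1% at b = 0. At 5, 10, 20 and 30% it is 23.2, 16.8, 11.1 and 8.5% for all cases, against 37.5, 35.8, 32.5 and 29.0% for new cases.

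**Where half the power is gone.** This happens at b of about 15% for the 15.5% rate and about 7% for the 8% rate.

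**Type I error.** With no effect, iC = iE, so pC = pE at any b and the test keeps its 5% level.

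**The case against.** A reader might infer that this outcome cannot show prevention at all. The documents do not support that. Randomisation balances earlier cases in expectation, the test keeps its level, and dilution acts only towards no difference, so a significant reduction would still support the aim.

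A reader might also infer that most of the power is lost. That depends on an entry share the protocol does not give. The loss runs from none to more than half over the range shown. Deep vein thrombosis is excluded at entry, and the interval between onset and inclusion is short for an infection to develop. The calculation borrows a urinary infection rate, although infection is missing from the tested list in section 6.2.1, and the larger entry shares are more plausible for swallowing than for infection. No single component is shown to have both figures. All this stands: the table shows direction and range, and does not forecast any component.

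The wording can be read more kindly. The exit item is limited to complications related to immobility, the three-month item speaks of what occurred during the stay, and section 2.2.2 also uses prevalence for side effects of sitting, which are plainly new events. That weakens the case for a deliberate count of earlier conditions, but neither collection item is tied to randomisation.

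Definitions can also be left to an analysis plan, and the case report form may hold more than the protocol lists. But section 6.2.6 has that plan written before database freeze. It can tighten a definition; it cannot recover baseline status that was not collected.

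Finally, power is modest even after the change, so a null result would still be inconclusive.

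**Conclusion.** The point holds as a loss of sensitivity, not of validity. The outcome and its test have no onset rule, and no listed item allows cases present at entry to be set aside for four of the five components in section 2.2.2. If 10% are affected at entry, power falls to about 41% instead of 63% for a complication with 15.5% new cases, and to about 17% instead of 36% for one with 8%. If nobody is affected, nothing is lost. At every non-zero share tested, counting new cases gave more power despite the smaller denominator.

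These figures rest on an assumed halving of new cases, on cited in-hospital rates used as new-case rates, and on an entry share that is not in the protocol. In my judgement the loss matters mainly for swallowing disturbance and catheterisation, and may be small for infections. As this is a secondary outcome without stated power, the change is worthwhile but does not touch the primary conclusion.

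Separately, the outcome list in section 2.2.2 names urinary tract infection where the test list in section 6.2.1 names acute urinary retention. The two do not agree.

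**What to change.** - In sections 2.2.2 and 6.2.1, and in the abstract, define each complication as new occurrence after randomisation, analysed among patients free of that complication at inclusion. The subset is defined by baseline status, so the randomised comparison is preserved.
- At the inclusion visit, add yes/no items for swallowing disturbance, pneumopathy, urinary infection and bladder catheter. Complete them before the envelope is opened, because the trial is open.
- Record an onset date for each complication.
- Keep overall prevalence during the stay as a description.
- In the same edit, reconcile urinary tract infection with acute urinary retention so that the outcome list and the test list match. If retention is kept, give it a baseline item too.

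The cost is four or five yes/no fields, one date per complication and a change of wording. The denominator for each component shrinks by the share affected at entry, for example from 200 to 180 per arm at 10%.

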### ***4.3. INCLUSION CRITERIA***

- Aged 18 or above
- Persistent neurological deficit at the time of inclusion, caused by a diagnosed ischemic stroke (defined by a sudden neurological deficit without hemorrhage on the CT.
- Patients hospitalized in a Neurology unit the same day or the day after the neurological deficit (provided that the patient was left with the upper body inclined at 30° maximum up to that time)
- Health coverage

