##### Length of stay

Duration between hospital admission and exit.

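### Immobility complications are defined as any-time prevalence in hospital with no baseline record, so conditions present before randomisation can count as outcomes and dilute the comparison

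*Protocol*

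**What the plan says.** The aim (section 2.2.1) is about prevention: "To show that early sitting decreases the rate of complications related to immobilization".

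The outcome (section 2.2.2) is "Prevalence of swallowing disturbances, pneumopathy, urinary tract infection, bladder catheterization, deep vein thrombosis during hospitalization". The analysis (section 6.2.1, and the abstract in the same form) compares "Prevalence of swallowing disturbance, pneumopathy, acute urinary retention, bladder catheterization, deep vein thrombosis during hospitalization" between arms by a chi-square or Fisher test. Nothing restricts the count to new events or to events after randomisation.

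On timing and recording:

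- Section 5.1.1 defines length of stay as "Duration between hospital admission and exit". This is the only definition of the hospital stay in the protocol.
- Section 4.3 admits "Patients hospitalized in a Neurology unit the same day or the day after the neurological deficit". Section 4.1 allows arrival through the emergency room or another unit. Under section 6.2.8 the envelope is taken once the patient is included.
- Section 5.2 collects "Immobility related complications during hospitalization" at hospital exit, and "Synthesis about complications that occurred during the hospital stay" at 3 months. It asks for no onset date.
- The inclusion visit in section 5.2 lists demographics, risk factors, history, symptoms, NIHSS, Rankin, Barthel and current treatments. It has no specific item for swallowing, catheter, urinary infection or pneumopathy.
- Section 4.4 excludes known or suspected deep vein thrombosis. It does not exclude the other four conditions, apart from breathing difficulty that could affect tolerance of sitting.
- Section 7.2 lists "Swallowing disturbances", and also pneumopathy, among events of the stroke itself.

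**The concern.** The aim concerns complications that a sitting schedule could prevent. The outcome, taken literally, asks whether a condition was present at any time between admission and discharge. A swallowing deficit caused by the stroke at onset, or a catheter placed in the emergency room, would be counted although neither procedure could have changed it.

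Such cases are equal between arms in expectation. They add the same share to both proportions, shrink the absolute difference and move the ratio toward 1. At stake is the ability to detect a preventive effect, which the introduction gives as part of the trial's hypothesis. The gap is partly one of data collection: if baseline status is not recorded, a later analysis plan cannot reliably separate old cases from new ones.

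**Working it through.** **The plan's own figure.** The protocol gives no sample size or power for this outcome. Its primary-outcome figure (35% v 50%, two-sided 5%, power 80%) was reproduced as a check on method. Without continuity correction, n = [1.96·√(2 × 0.425 × 0.575) + 0.8416·√(0.35 × 0.65 + 0.50 × 0.50)]² / 0.15² = 169.3. With the correction, n = (169.3/4)·[1 + √(1 + 4/(169.3 × 0.15))]² = 182.4, so 183 per group, as stated in section 6.2.2. That figure is not in dispute.

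**Inputs for the dilution**

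- 200 per arm: 400 patients, 1:1 (sections 6.2.2 and 6.2.8).
- New-event risk in the progressive arm: 15.5%, the urinary infection rate cited in section 1.1, used here as a scale rather than as a forecast for each condition. A second scenario uses 10% (assumed).
- Effect: new events halved (assumed).
- Share b already affected at randomisation: not in the protocol, so a range is shown.

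**Formulas**

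- Observed proportion in an arm, all cases counted: b + (1 − b) × new-event risk.
- The difference shrinks by the factor (1 − b).
- Power = Φ[(d − 1.96·SE₀)/SE₁], with SE₀ pooled and SE₁ unpooled.
- New events only: the same formula with 200 × (1 − b) patients per arm and the undiluted risks.

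**Worked case, b = 10%, 15.5% v 7.75%**

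- All cases: 0.10 + 0.90 × 0.155 = 0.2395, against 0.10 + 0.90 × 0.0775 = 0.16975. Difference 0.06975, risk ratio 0.71. SE₀ = 0.04034 and SE₁ = 0.04019, so (0.06975 − 1.96 × 0.04034)/0.04019 = −0.232 and power is 41%.
- New events only, 180 per arm: SE₀ = 0.03379 and SE₁ = 0.03354, so (0.0775 − 1.96 × 0.03379)/0.03354 = 0.336 and power is 63%. Risk ratio 0.50.

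**Range**

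| b | 15.5% v 7.75%: apparent ratio | Power, all cases | Power, new only | 10% v 5%: apparent ratio | Power, all cases | Power, new only |
|---|---|---|---|---|---|---|
| 0% | 0.50 | 68% | 68% | 0.50 | 48% | 48% |
| 5% | 0.63 | 52% | 66% | 0.67 | 31% | 46% |
| 10% | 0.71 | 41% | 63% | 0.76 | 22% | 44% |
| 20% | 0.81 | 27% | 58% | 0.86 | 15% | 40% |

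At b = 2%, with 15.5% v 7.75%, the powers are 61% and 67%. At the 8% pneumopathy rate cited in section 1.1, halved, they are 17% and 36% at b = 10%.

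**The case against.** **The protocol never says that pre-existing cases count.** This stands. The inference rests on the word prevalence, the absence of a new-onset rule and the absence of a baseline record. The protocol also uses prevalence for side effects of sitting, which can only be new, and the 3-month item speaks of complications that occurred. A reader who takes that item to mean new events is not unreasonable. Even so, the window is the hospital stay, so events between admission and randomisation would still count, and the outcome and analysis sentences carry no restriction.

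**Other documents may settle it.** Section 6.2.5 is silent here, but section 6.2.6 announces an analysis plan and the eCRF is not shown. Section 7.1.1 also requires harmful events during the study to be documented, which would give some post-inclusion recording. The counting rule could properly go in the analysis plan. None of this supplies baseline swallowing or catheter status, which the protocol's list of inclusion data omits.

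**The size is assumed.** Also true. Inclusion comes within about a day of onset, and some breathing difficulty is excluded, so b is probably low for pneumopathy and urinary infection; at b = 2% the loss is 6 points. A large b is arguable only for swallowing disturbance and catheterisation.

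**Two stronger readings are tempting, and neither is supported.** One is that the comparison is biased toward an arm. Randomisation balances pre-existing conditions in expectation, so the effect is attenuation. The other is that this definition is why a real reduction would be missed. With 10% v 5%, power is only 48% even when nobody is affected at baseline, because the trial was sized for the Rankin outcome.

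**Conclusion.** The concern holds as a point about some components of one secondary outcome. As worded, the outcome can include conditions that predate allocation, and the listed inclusion data would not allow them to be removed reliably. The result is dilution and lost power.

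If new events are halved from 15.5%, counting all cases costs 14 points of power at b = 5%, 22 at b = 10% and 31 at b = 20%. From 10%, it costs 15, 22 and 25 points. Both b and the halving are assumptions. The direction of the effect rests on one further premise, that the procedures cannot change a condition already present.

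Deep vein thrombosis is largely protected by its entry exclusion. The primary outcome is untouched. The point merits correction because the remedy is cheap and missing baseline status is hard to recover later.

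**What to change.** 1. At the inclusion visit (section 5.2), before the envelope is opened, record yes or no for swallowing disturbance, bladder catheter, urinary infection and pneumopathy.
2. In sections 2.2.2 and 6.2.1 and the abstract, define each outcome as a new event after randomisation among patients free of that condition at inclusion. Baseline status precedes allocation, so this restriction keeps the randomised comparison. Record the onset date of each complication.
3. Keep any-time prevalence as description.
4. While editing these sentences, reconcile the two lists: section 2.2.2 names urinary tract infection where section 6.2.1 names acute urinary retention. If retention stays, record it at inclusion too.

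Cost: four tick boxes (five with retention), onset dates on the complication form and a revised sentence in each place. Each comparison loses the patients already affected, for example 180 instead of 200 per arm at b = 10%. Power remains modest after the change, so non-significant results here should still not be read as absence of effect.
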